## Abstract

**Background:**

Mobile-based screening interventions to detect and treat Major Depressive Disorder (MDD) at an early stage might be a promising approach for reducing its societal burden. In the present study, we will evaluate the feasibility and effectiveness of screening for MDD using a mobile-based screening protocol.

**Methods:**

This study will be a three-arm, parallel randomized control trial (RCT) performed in a multi-ethnic population within the municipality of Rotterdam (the Netherlands). The trial includes two intervention groups that will be screened 4-weekly for MDD for 12 months using the Patient Health Questionnaire (PHQ-9) and a control group who does not receive mobile-based screening for MDD. Participants in the one-test intervention arm will be referred for further diagnosis and treatment, if necessary, after a single positive test score for moderate-severe major depression symptoms (PHQ-9 > 10). Participants in the multiple-test intervention arm will only be referred after three consecutive positive test scores. 1786 eligible participants will be included in the RCT, with 446 and 447 in the one-test and multiple-test referral arms, respectively, and 893 in the control arm. Primary outcome is participants’ QoL after 12 months (EQ-5D-5L). Secondary outcomes include participants’ QoL after 24 months (EQ-5D-5L), evaluating the occurrence and severity of MDD symptoms (PHQ-9), intervention engagement, and identifying public mental health differences based on sociodemographic characteristics, including age, gender, ethnicity, financial situation, educational background, and living area. Long-term results of the RCT will be incorporated into a microsimulation model to determine the long-term benefits, harms, and costs of MDD screening.

**Discussion:**

The information gained from examining the feasibility and (cost-) effectiveness of mobile-based screening for MDD could be of guidance for mental health policy implementations and support the introduction of mobile-based screening for MDD in the Netherlands and/or other nations.

**Trial registration:**

ClinicalTrials.gov: NL84280.078.23, NCT05989412, August 8, 2024.

**Supplementary Information:**

The online version contains supplementary material available at 10.1186/s40359-024-02230-6.

## Introduction

### Background

Major depressive disorder (MDD) is a common mental disorder, affecting more than 264 million people worldwide [1, 2]. MDD is the fourth-largest contributor to the global disease burden and the leading cause of disability worldwide [3]. The global prevalence of MDD is estimated to be 13%, which varies by age and gender, as well as socio-economic status [4]. Recurrences following an initial depressive episode are particularly problematic, with an estimated probability of 75 to 90%, because they often lead to a more severe course of illness, increased resistance to treatment, and greater overall impairment [5]. Consequences associated with MDD are widely spread: MDD is linked to a reduced (healthy) life expectancy and severely diminishes an individual’s Quality of Life (QoL), affecting their personal relationships, work life, and general health [1, 6, 7]. The total economic impact of MDD in the European Union is estimated to be more than 100 billion euros per year [8].

Given the long-term and recurrent nature of MDD and its numerous negative consequences, secondary prevention, alongside primary prevention, may be significantly important [9]. Secondary prevention of MDD relies on the early detection of individuals at risk, followed by timely and appropriate interventions to address symptoms before they develop into full depressive episodes. By intervening early, it is possible to alter the course of MDD, minimizing the chronic nature of the disorder and lowering the overall disease burden [10]. Screening can play a key role in timely identifying MDD, particularly in high-risk groups, who are unlikely to seek help or do not recognize symptoms of depression. A number of validated screening methods are available, and screening for depression is already recommended in several healthcare settings and population subgroups [11, 12]. In this study, we will use the Patient Health Questionnaire-9 (PHQ-9), a widely validated questionnaire for MDD screening, to detect depressive symptoms [11]. Previous studies suggest that screening may effectively reduce MDD symptoms and significantly increase remission rates [13].

The use of mobile-based screening tools presents an innovative approach to enhance MDD screening and improve mental health outcomes in managing MDD. Mobile-based interventions have the advantage of accessibility, scalability, convenience, and real-time data collection making them particularly suitable for populations that are less likely to engage with traditional healthcare [14–16]. While the potential for secondary prevention of MDD is expected [17–19], the effectiveness of mobile-based screening for MDD in the general adult and ethnically diverse population has not yet been shown. The present study aims to determine the feasibility and effectiveness of screening for MDD by providing a mobile-based screening protocol using a randomized controlled trial (RCT). The present trial will be the first experimental mobile-based screening intervention on MDD for the general, multi-ethnic adult population. We hypothesize our approach could provide new insights into early detection strategies and improve outcomes by reaching a broader and more diverse population, thereby offering scalable and flexible options for addressing the global burden of MDD.

### Objectives and hypothesis

This RCT assesses the feasibility and effectiveness of mobile-based screening for MDD in the adult population of Rotterdam, mainly the Southern part of the city. The primary aim is to compare changes in participants’ QoL between baseline and after 12 months in the screening versus those of the non-screening group. Secondary objectives involve measuring the occurrence and severity of MDD symptoms and quantifying the impact of screening in population subgroups. Additionally, the study aims to evaluate the long-term effects of MDD screening by measuring participants’ QoL after 24 months. These objectives will help to better understand the broader impact of mobile-based screening on mental health outcomes. A better understanding of the feasibility and effectiveness of mobile-based screening for MDD may be of guidance for mental health policymakers and may provide evidence for implementing MDD screening interventions.

We hypothesize that a mobile-based screening strategy for MDD will substantially reduce the burden of MDD over time, improve participants’ QoL, and minimize disparities associated with MDD.

## Methods/design

### Study design and setting

The MOOD (MObile-Based Screening fOr Depression) study is designed as a prospective, randomized controlled multi-arm trial with three parallel groups: a control group and two different intervention groups. We developed the MOOD intervention program by incorporating expertise from various stakeholders, including citizens and experts in mental, digital and public health. After completing a short survey to check for inclusion and exclusion criteria and the digital informed consent procedure, randomization will be performed at the individual level in a 2:1:1: ratio for the control group and the two intervention groups respectively. Participants in the control group will not receive mobile-based screening for MDD, while those in the two intervention groups receive a screening test using the PHQ-9 questionnaire at four-week intervals over a 12-month period. The intervention groups will be divided into two arms. In the one-test referral arm, participants who score positive for moderate to severe depressive symptoms (PHQ-9 score > 10) on a single screening will be referred for further diagnostic evaluation and treatment if necessary. In the multiple-test intervention arm, participants will only be referred for further diagnostic evaluation and treatment after three consecutive positive screenings indicating moderate to severe depressive symptoms (PHQ-9 score > 10). For the screening process in this study, we utilized a Clinical Trial Management System (CTMS) software developed by Your Research [20]. The application enhances efficiency by automating research processes such as data management, workflow optimization, and real-time reporting to ensure consistency and compliance throughout the study. Key features include error reduction, robust data encryption, comprehensive audit trails, ensuring data integrity and regulatory compliance. Participants can use this application at any moment to complete the survey(s). If any questionnaire is not finished after three days, participants will receive a reminder via email or push notification, depending on personal preferences. A second reminder will be sent after ten days. This allows participants to remain engaged and adhere to the study timeline. All study materials, including the website, questionnaires, Patient Information Form (PIF), and Informed Consent (IC) form, will be accessible in six languages: Dutch, English, Turkish, Spanish, Polish, and Arabic and will be provided in B1 language proficiency level. These languages were selected to ensure broad accessibility and inclusivity, reflecting the diverse linguistic backgrounds of the study population. Additionally, the questionnaires themselves will be available in 12 languages to further ensure the validity of the responses across the diverse population. The trial will be conducted by the Department of Public Health at the Erasmus University Medical Center Rotterdam, the Netherlands. The intervention area will focus on Rotterdam, particularly on the Southern part of the city, namely the districts Charlois, Feijenoord, and Ijsselmonde. The population in these districts is ethnically and socioeconomically diverse, with more than 90% having origins outside of Dutch heritage and more than 20% is unemployed [21]. It is expected that in this region there will be an above average prevalence of MDD, which will increase the screening’s potential impact and allow for better measurement [1, 6, 19]. This study is evaluated and approved by the Central Committee on Research Involving Human Subjects (CCMO) of the Netherlands (reference: # NL84280.078.23). The study is registered at the ClinicalTrials.gov Protocol Registration and Results System (ID = NCT05989412).

### Participants

We aim to include 1786 participants. Inclusion criteria are (1) be at least 18 years old; (2) live in the municipality of Rotterdam; (3) have access to a computer or smartphone; and (4) being able to complete the questionnaires in one of the provided languages. Exclusion criteria are (1) currently receiving therapy from a psychologist or psychiatrist for depressive symptoms; or (2) having been referred to a psychologist or psychiatrist in the past year for depressive symptoms. Eligibility screening will be conducted through the study’s website, after which participants will digitally sign the consent form via email. This will be followed by a baseline assessment completed through the application.

### Evaluation instruments

Evaluation instruments applied in the study are the PHQ-9 for measuring symptoms of depression and the 5-level EuroQol-5D (EQ-5D-5L) for assessing QoL, providing a comprehensive overview of the participants’ health status.

The *PHQ-9*, a widely used screening tool for detecting depression symptoms, is a validated and reduced version of the PHQ [11], which scores each of the 9 DSM-IV criteria as ‘0’ (not at all) to ‘3’ (nearly every day). As a severity measure, the overall score can range from 0 to 27, calculated by summing the scores for each question. Total scores of 5, 10, 15, and 20 represent the thresholds for mild, moderate, moderately severe and severe depression, respectively. MDD is suggested if ≥ 5 out of 9 items have been present at least ‘more than half the days’ in the past two weeks [11]. A PHQ-9 score ≥ 10 will be used in this study as referral advice threshold. This threshold has been shown to have a sensitivity of 88% and a specificity of 88% for MDD [11]. One of the 9 symptom criteria (“thoughts that you would be better off dead or of hurting yourself in some way”) counts as major depression if present at all, regardless of duration. In response to question 9, participants who select “more than half the days” will receive an additional notification including suicide prevention information. Given that the questionnaire depends on patient self-report, a healthcare professional should verify questionnaire outcomes and provide participants with diagnosis and further treatment if necessary. The PHQ-9 has been validated in the languages used in this study, including Dutch [22], English [11], Spanish [23], Polish [24], Turkish [25], and Arabic [26]). The English version of the PHQ-9 can be found in an additional file (see Additional file 2).

The *EQ-5D-5L* is being used as a 5-item self-report validated questionnaire for assessing health and health-related QoL across five core dimensions (5D): mobility, self-care, daily activities, pain/discomfort, and anxiety/depression and has been widely used to measure the QoL [27]. Items are scored on zero-five levels of severity (5L) for each dimension. Higher scores represent decreased QoL on that day [27]. The EQ-5D-5L can be found in an additional file (see Additional file 3). The EQ-5D-5L also includes the *EQ visual analogue scale* (EQ VAS), which captures participants’ self-rated health on a vertical visual analogue scale with endpoints labeled as’The best health you can imagine’ and ‘The worst health you can imagine’. The EQ VAS will be utilized as a quantitative measure of health outcome, reflecting the participants’ daily health-state perceptions [27]. The EQ VAS can be found in an additional file (see Additional file 3). The EQ-5D-5L has also been validated in the languages applied in this study, including Dutch [28]), English [29], Spanish [30], Polish [31], Turkish [32] and Arabic [33].

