### Procedure

Participants will be recruited through different online and offline strategies to encourage citizens’ participation according to different cultural backgrounds. This approach ensures inclusivity and reflects the diverse population we aim to engage in the study. Offline recruitment includes in-person interactions with community members called “key figures”, video promotion, presentations and personally addressing people in public areas. Online recruitment efforts will include websites, social media networks, and local newspapers. By utilizing both digital and physical recruitment strategies, we aim to maximize reach and engagement. Interested individuals can enroll by initiating an application procedure through the study’s website [20], where they will complete an application form to assess eligibility. Eligible participants will then be invited to create a secure personal account and will be provided with a digital patient information form (PIF) and a digital informed consent (IC) form (see Additional file 1). The IC procedure is conducted digitally using Valid Sign, a digital signature platform that enables secure signing of documents online and streamlines the consent process. In line with our aim of ensuring simplicity and accessibility, an invitation email will provide instructions on downloading the Your Research CTMS application to their tablet or smartphone. This application will serve as the primary platform for all study related activities. Results will be sent directly to the server and will be accessible to participants at any time through the app. There will be a variety of platforms provided for additional inquiries about the study procedures including mail, WhatsApp or phone calls. Participants who complete and return the signed e-consent form will be enrolled and randomized in the trial. Depending on their assigned intervention arm, participants will be required to fill in questionnaires, sent via the Your Research app, within two weeks. To ensure adherence, push notifications will be sent to participants who do not complete the questionnaire within 3 days. Participants can choose their preferred notification method, which may include email, SMS, or application notifications. The data collection will run for 24 months. Participants, including those in the control group, will complete the EQ-5D-5L questionnaire via the Your Research CTMS application at baseline (0 months), and at 6, 12, and 24 months. Recruitment will be closely monitored to ensure that the target sample size is achieved. Once the sample size is reached, inclusion will be stopped. Participants will receive compensation at the end of the study based on the number of completed questionnaires, with a maximum of €50 (paid in gift cards). Additional vouchers may be earned by inviting more participants via the app. Participants can withdraw from the study at any time during the trial. To address any logistical or general MDD-related queries, participants can visit the study website [20] or contact the researchers by e-mail or WhatsApp. Additionally, a phone line will be available for inquiries on weekdays, staffed by Erasmus MC MOOD study researchers. To ensure participant safety, the program includes specific measures for addressing potential risks. For example, if questionnaire responses indicate severe depressive symptoms or a risk of self-harm, participants will be immediately directed to appropriate crisis support resources, such as ‘De Luisterlijn’ or ‘113 suicide prevention’ [34]. Additional information on suicide prevention and emergency contacts will be provided as needed, based on the assessment results. These safety measures are crucial for addressing any emerging mental health concerns in real-time, ensuring participant well-being throughout the trail.

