### Sample Size

In this study we compare the control group with both combined intervention groups with one-test referral for further diagnosis and treatment, and with multiple-test referral follow-up for further diagnosis and treatment. A total of 1,428 participants are required for the study, utilizing a 2:1:1 randomization scheme. This sample size will provide 80% power to detect a difference corresponding to an improvement of 0.40 in QoL. Additionally, frequent screening is expected to be effective in 40% of participants diagnosed with MDD, with a significance level set at 5% [30, 36–38]. Furthermore, a cumulative incidence of MDD during 12 months of 10% was assumed in our high-risk population [27, 39, 40]. These numbers lead to an expected difference in QoL of 0.016 at 12 months between the screening and control groups. A standard deviation of 0.18 in the score of the EQ-5D-5L in the general population has been expected [30, 41]. In the analysis, adjustments were made for the baseline EQ-5D-5L, assuming a correlation coefficient of 0.8 between the baseline measurement and the measurement at 12 months [42]. The design effect for adjusting for the EQ-5D at baseline is hence 0.36. As a result, calculating the sample size using the design effect for a two-sample t-test indicates that 714 participants are required in the control arm and combined intervention arms. To compensate for the potential 20% loss [43] of follow-up in both arms, we aim to recruit an additional 179 participants for the control arm and 179 participants for the intervention arm (1:1 between both intervention groups). To reach our goal we therefore need to include 1,786 participants in total.

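### The item-9 suicide-prevention trigger lacks 'at least', so as written it omits the most severe answer (minor safety wording)

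*Protocol article*

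**What the plan says.** Three statements in Evaluation instruments bear on the point. The item scale: the PHQ-9 "scores each of the 9 DSM-IV criteria as ‘0’ (not at all) to ‘3’ (nearly every day". The symptom-count rule for suggesting MDD: at least five of the nine "items have been present at least ‘more than half the days’ in the past two weeks". The safety trigger: "In response to question 9, participants who select “more than half the days” will receive an additional notification including suicide prevention information". The same paragraph also says that item 9 counts towards major depression at any frequency.

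The Procedure section adds two general safety statements: "if questionnaire responses indicate severe depressive symptoms or a risk of self-harm, participants will be immediately directed to appropriate crisis support resources", and "Additional information on suicide prevention and emergency contacts will be provided as needed, based on the assessment results". Neither gives an item-9 answer or score as a cut-off.

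The rule matters wherever the PHQ-9 is answered. That includes the two intervention arms, which "receive a screening test using the PHQ-9 questionnaire at four-week intervals over a 12-month period".

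**The concern.** The trigger names one answer on an ordered scale, and that answer is not the top one. A safety rule of this kind is normally a threshold, met by the named answer and everything above it. As worded, a participant who reports thoughts of death or self-harm nearly every day does not meet it, while one who reports them less often does.

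It is the only place in the article where an item-9 answer is tied to an action. Someone building, auditing or copying the procedure would take the rule from here. What would be lost is the additional notification for the participants with the most frequent thoughts. This is a point about participant safety and clear wording. It has no bearing on the estimate of the screening effect.

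**Working it through.** The article gives no figure to reproduce. The check is to set the statements side by side.

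**1. Is the top answer distinct from the named one?** Yes. Evaluation instruments gives 'nearly every day' as score 3, so the named answer is a different and lower category. The article does not print a score beside 'more than half the days'. Score 2 is inferred from its place just below the top of the 0-3 scale, and it can be checked against the questionnaire in Additional file 2. The defect does not depend on this inference, but a fix expressed in scores does.

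**2. Which answers meet the rule?**

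| Item-9 score | Rule as written | Rule with 'at least' |
|---|---|---|
| 0 (not at all) | no | no |
| 1 | no | no |
| 2 (more than half the days) | yes | yes |
| 3 (nearly every day) | **no** | yes |

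The two readings differ in one row, the most severe answer.

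**3. Does the article write thresholds elsewhere?** Yes. The symptom-count rule uses the same answer category with 'at least', a few sentences before the trigger. The contrast makes the missing words visible. It also suggests an oversight, since nothing in the article gives a reason for notifying at the lower answer and not at the higher one.

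**4. Does other text supply the missing category?** In part. The two Procedure statements would naturally cover someone with such thoughts nearly every day. They set no item-9 cut-off and do not restate the trigger, so they reduce the consequence but leave the wording uncorrected.

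**5. Does referral fill the gap?** Not reliably. Referral depends on the total score, with a threshold of about 10 (the article writes it both as above 10 and as 10 or more). Item 9 contributes at most 3 of 9 x 3 = 27 points, so the top answer alone does not reach the threshold. In the multiple-test arm, referral needs three positives in a row at four-week spacing, so at least 2 x 4 = 8 weeks separate the first positive from the third.

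**The case against.** The strongest reply is that no sensible reader would apply the sentence literally. There is no clinical reason to notify at the second-highest answer and stay silent at the highest, so the intended meaning is clear. The Procedure section also promises crisis resources and suicide-prevention information to anyone whose responses suggest a risk of self-harm, which is much the same content as the notification. And this is a condensed article: the exact item logic would normally sit in the full protocol or the app specification, neither of which is shown.

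Most of this stands. The problem is very probably a slip. A reader might infer that the investigators chose to exclude the top answer, or that participants giving it would receive no safety response. The article supports neither: no rationale for an exclusion appears, and the Procedure text plausibly reaches these participants.

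The reply does not remove the point, however. The article does more than leave a detail to another document. It states an explicit trigger and states it wrongly. The general Procedure text has no cut-off against which an implementation could be checked, so the only item-specific rule in print remains the faulty one.

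**Conclusion.** The point holds as a minor correction to safety wording. The stated trigger literally leaves out one of the four answer categories, and that category is the most severe. What is at stake is the additional notification alone. No sample size, power, error rate or trial result is affected.

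The conclusion rests on a literal reading of one sentence and on 'nearly every day' being a separate, higher category, which the article states. It does not rest on how the app behaves, which the article does not show. A reader might infer that the app applies the rule automatically as printed. The article describes automation of research processes in general terms, under Study design and setting, and says nothing about this rule.

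A reader might also be tempted to turn the number of participants and screening rounds into a count of missed notifications. The documents do not allow it. They give no share of participants choosing the top answer. Any such count would also need the app to be coded to fire at the named answer only, which is improbable. In addition, the Statistical analysis section expects that whole questionnaire rounds may be missed, so scheduled rounds are not completed ones.

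**What to change.** In Evaluation instruments, insert 'at least' before the named answer, so that the notification goes to participants with an item-9 score of 2 or 3. Confirm that the app logic uses item 9 >= 2, and correct it if it does not.

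While making the change, the investigators could state whether a threshold of 2 is what they want, because the same paragraph counts item 9 at any frequency and any non-zero answer would be an alternative trigger. That is a clinical decision for them and is not needed to correct the wording.

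The cost is two words and one check of the software, with no change to the design, sample size or analysis.
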